# SUMMARY

**Background:**

The largest group of visual disorders after acquired brain injury are homonymous visual field defects (HVFDs). It has been estimated that 20-30% of all patients with stroke have HVFDs [1] and that 70% of these patients show a spatially disorganized visual search strategy and disturbed visual exploration of the surroundings, impairing daily mobility-related activities [2]. As a consequence, they often fail to notice relevant objects or avoid obstacles and they are often unable or afraid to walk or cycle independently. This has far-reaching, disabling repercussions on their domestic and vocational lives and participation in society. However, when patients become aware of their deficits and learn to apply a new scanning strategy in order to compensate for the visual field defect, daily life mobility may be improved substantially [3,4]. In a recently published systematic review [3], it was concluded that compensatory scanning training is the most promising approach when it comes to the level of participation in society. This training teaches patients to apply large eye and head movements towards the blind hemifield. The patient learns to enlarge the functional field of view and to compensate for the loss of visual information that would occur if no eye movements were made.

First evidence for the effects of compensatory scanning training has been found, but the training protocols that were examined differed from each other and so far, few attention has been paid to the effects on mobility. Furthermore, only studies using within-patient repeated measures designs have been performed. The randomised controlled trial (RCT) as proposed in this study protocol provides a solution for these problems.

**Aim:** The aim of this study is to examine the effect of a compensatory scanning training. The effects will be investigated on the level of functions, activities and participation. Furthermore, the predicting effects of several variables will be examined.

**Study design:** Single-blind controlled intervention study

**Study population:** Patients with HVFD (hemianopia or quadrantanopia) due to acquired brain injury, age 18-75.

**Intervention**: All participants will receive scanning training according to a protocol at Royal Dutch Visio, Centre of Expertise for Blind and Partially Sighted People.

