### 6.1.2. Secondary outcome measures

*Visual functions:*

- Visual field, with Goldmann (2x monocular)
- Visual acuity, with ETDRS 2000 letter chart at 500 lux
- Contrast sensitivity, with Gecko at 500 lux

*Questionnaires (see also F1.Questionnaires)*:

- Awareness; based on theories on awareness by Crosson [7] and Critchley [8] and piloted in a group of patients with hemianopia.
- Life events; questions based on the Life Events Questionnaire (LEQ) [9].
- Motivation; questions selected from Motivation for Traumatic Brain Injury Rehabilitation Questionnaire (MOT-Q) [6].
- Expectations/Evaluation of training; questions based on interviews from previous master thesis research at UMCG Beatrixoord.
- NEI-VFQ25 (National Eye Institute - Visual Functioning Questionnaire/25 items, Dutch translation)
- VOM (Vragenlijst Onafhankelijke Mobiliteit, Dutch translation of the Independent Mobility Questionnaire)
- CVD (Cerebrale Visuele Stoornissen, Dutch translation by M. L. M. Tant, 1997)

*Neuropsychological testing:*

- Grey Scales
- NLV (Nederlandse Leestest voor Volwassenen)
- Zoo-map (BADS)
- 15-Words Test

*(Ecological) scanning and mobility tests:*

- Dot Counting Task (with eye tracking); dots are presented on a large screen and are to be counted by the patients.
- Standardized search task (with eye tracking); search task on a large screen; patients have to indicate whether or not a target is present among distractors.
- Hazard perception pictures (with eye tracking); photos of traffic situations; patients have to indicate what action they would perform in the given situations: brake, release gas pedal or do nothing.
- Hazard perception movie clips (with eye tracking); short movies of traffic situations; patients have to indicate which overt and covert hazards are present.
- Tracking Task; test in which the patient tries to keep an imaginary car on the road in the presence of cross wind using a steering wheel (road is depicted on a central monitor) while simultaneously reacting on stimuli in the left and right periphery.
- Rides in a driving simulator
- Mobility test; walking through a corridor, with and without obstacles and with and without a cognitive dual task (digit span).

*Test for cross validation:*

- Reading test

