Clarification: the questionnaires are used to examine the outcome on the activity and participation level: the NEI-VFQ25 (National Eye Institute - Visual Functioning Questionnaire/25 items), the VOM (Vragenlijst Onafhankelijke Mobiliteit) and the CVS (Cerebrale Visuele Stoornissen). Change in participation is also measured with the evaluation questionnaire in the post-assessment, based on evaluation questionnaires from UMCG-Beatrixoord. Finally, also the session reports from the therapists are deployed for this aim.

*Fitness to drive as outcome parameter:*

Most patients with hemianopia are not allowed to drive a car. The Netherlands are one of the few countries worldwide where patients with hemianopia can be declared fit to drive by the CBR by succeeding a special test of practical fitness to drive. In order to apply for such a driving test, the so-called ‘Eigen Verklaringsprocedure’ (www.cbr.nl) has to be followed. Every person with hemianopia has the right to apply for this procedure.

In the existent rehabilitation program ‘AutO-Mobility’, Royal Dutch Visio guides patients with visual disorders in safe and independent participation in motorized traffic. It is a close collaboration with the CBR, a number of certified driving schools, and the departments of Ophthalmology and Neuropsychology from the UMCG. Naturally, participants in this study also have the right for independent participation in motorized traffic. They may therefore not be abstained from this information. In practice, this indeed appears to be a frequent need in this population. Because training or driving lessons related to the program AutO-Mobility might interfere with the research program here proposed, both trajectories have to be carefully aligned in an early stage. This yields possibilities for examining the effect of scanning training on regaining a drivers’ license. Part of the participants in this study perform a test of practical fitness to drive at the CBR before and after scanning training. Based on these results, Visio and the CBR will decide on including the scanning training in the Eigen Verklaringsprocedure for people with hemianopia.

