When the waiting list is longer than 10 weeks, the patient will be allocated to either the training group or the control group based on the random allocation described above. When the waiting list is shorter, which is not expected, the patient will be allocated to the training group in case the patient belongs to this group based on the random allocation. In case the patient would belong to the control group based on the random allocation, the patient is excluded from the study, but the patient can still start scanning training within 10 weeks. Patients from both the training group and the control group will visit the University Medical Center Groningen for a pre-assessment (the week before onset of training at Royal Dutch Visio) and a post-assessment (after 10 weeks of training). The control group will participate in a third assessment, 10 weeks before the pre-assessment. (the so-called -10 assessment). By looking at the results from the pre-assessment and post-assessments of the training group and the results from the -10 assessment and pre-assessment of the control group, the effect of 10 weeks of training is compared to the effect of 10 weeks on the waiting list. In addition, the effect of treatment on the individual level can be examined by comparing the results from the post-assessment to the results from the -10 assessment and pre-assessment in the control group (within-patient repeated measures design). Including the post-assessment in the control group also increases power of the study.

The effect measurements will be performed by (student) neuropsychologists under supervision of [name]. They are not informed about the allocation to the training group or the control group and therefore they do not know whether the patient already received training or not.

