## 6.3. Study procedures

For the evaluation of inclusion, patients take part in a regular admission interview, visual function assessment, low vision assessment and neuropsychological assessment at Royal Dutch Visio in the nearest region. Participants will visit the UMCG two or three times (depending on the research group) for the effect measurements. The tests and assessments including in the effect measurements are described in section *6.1.2. Secundary outcome measures.*

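### Section 6.2 infers assessor blinding from not disclosing the allocation, but the post-assessment training evaluation and the arm-dependent visit schedule leave routes to unmasking that the protocol does not close

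*Protocol*

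**What the plan says.** The Summary describes the trial as a "Single-blind controlled intervention study". The only masking described is that of the assessors, in Section 6.2. Neuropsychologists or student neuropsychologists carry out the measurements without being told which group a patient is in, and from this the protocol concludes: "therefore they do not know whether the patient already received training or not".

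Section 6.3 defines what is measured at the hospital visits: "The tests and assessments including in the effect measurements are described in section", and the section it names is 6.1.2. That section lists, among the questionnaires, "Expectations/Evaluation of training; questions based on interviews from previous master thesis research at UMCG Beatrixoord". Its clarifying paragraph gives the timing of one part: "Change in participation is also measured with the evaluation questionnaire in the post-assessment".

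Sections 3 and 6.2 set the visits. Both groups have a pre-assessment in the week before training and a post-assessment after 10 weeks of training. Controls have one more assessment, 10 weeks before the pre-assessment. Section 6.3 confirms two or three visits, depending on group. Section 8.2 compares the groups at T2, possibly corrected for T1, and within controls compares the T1-T2 change with the T2-T3 change.

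**The concern.** Not being told the allocation is one safeguard; it does not ensure ignorance of training status. The assessor can also learn that status from what happens in the session or from which visit it is. Here both carry information about the arm, and the protocol describes nothing that keeps it from the assessor.

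Assessor masking carries more weight than usual in this trial. Patients know whether they have been trained. Section 6.1.1 concedes that controls receive no placebo intervention and that a non-specific effect cannot be fully excluded. If the assessors also know, none of the masking described behind the single-blind label remains, and examiner-run tests become open to differences in instruction and encouragement between the arms.

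**Working it through.** The point rests on setting the sections side by side.

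**Step 1: training status at each visit.** Section 8.2 does not define T1 to T3. The mapping below follows from the schedule in Sections 3 and 6.2, with visits numbered in time. (Section 6.2 uses the word third for the extra control assessment, which is first in time.) Counts use the 30 per group of Section 4.4.

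| Visit in time | Training group | Control group | Trained / untrained |
|---|---|---|---|
| T1 | pre-assessment, untrained | -10 assessment, untrained | 0 / 60 |
| T2 | post-assessment, trained | pre-assessment, untrained | 30 / 30 |
| T3 | no visit | post-assessment, trained | 30 / 0 |

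Total visits: 60 + 60 + 30 = 150.

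**Step 2: what visit number reveals.** It fixes training status at T1 and T3, that is at (60 + 30) / 150 = 60% of visits. The 60 visits at T1 are no defect, since any trial with a baseline has them. That leaves the 30 at T3 (30 / 150 = 20%), which enter only the within-control comparison of changes. At T2 visit number reveals nothing, so masking is possible there, and T2 is where the between-group contrast lies.

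**Step 3: what session content reveals at T2.**
- The assessors perform the effect measurements (6.2).
- The effect measurements are the 6.1.2 battery (6.3).
- The battery includes the training questionnaire, and its evaluation part is given at the post-assessment (6.1.2).
- At T2 only the training group is at its post-assessment (Step 1).

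The evaluation part therefore belongs to 30 of the 60 T2 sessions, all in one arm. Whoever gives or sees it knows the arm.

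**Step 4: stated safeguards.** The protocol describes no separate person for the questionnaire, no rule that it comes after testing, no withholding of visit number, no request to patients not to mention training, and no masked processing of recordings.

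**Step 5: size.** The document contains no figure from which a bias could be derived. Purely as a scale, suppose an assessor-induced shift of d standard deviations in favour of training, with no true effect, 30 per group and an unadjusted one-sided t-test at 0.05 (58 degrees of freedom, critical value 1.672). The noncentrality is d × √(30/2):

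| Assumed d | Noncentrality | False-positive rate |
|---|---|---|
| 0 | 0 | 0.050 |
| 0.05 | 0.194 | 0.073 |
| 0.10 | 0.387 | 0.103 |
| 0.20 | 0.775 | 0.190 |

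The values of d are assumptions, and correction for T1, which Section 8.2 allows, would change the figures.

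**The case against.** The strongest reply is that the protocol does not say who hands out the questionnaire, when in the day, or whether the assessor sees it. Section 6.1.2 points to a questionnaire annex that is not at hand. If patients complete the form alone and give it to a coordinator, the main route closes. Nor does listing in 6.1.2 prove that an assessor administers an item: the same section covers therapists' session reports and the practical driving test at the licensing authority, which the hospital assessors plainly do not perform. This stands. A reader might infer that blinding demonstrably fails at every T2 visit; the text shows only that the claim does not follow and is unprotected.

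Three further inferences are tempting but unsupported. One is that controls receive the expectations part at T2: only the evaluation part is timed. Another is that assessors pace and partly score the tasks: Section 6.1.2 describes the tasks, not how they are paced or scored. The third is that the primary result is compromised: the primary outcome is fixation and saccade parameters recorded by eye tracker on the Dot Counting Task, which an assessor can influence much less.

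The visit-number route is also limited. It requires the assessor to know the visit number, which is not stated, and it does not reach the between-group contrast.

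What survives is that the protocol makes a positive claim about masking, and its own schedule and battery, followed as written, undermine it. This is study conduct, not a detail normally left to an analysis plan.

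**Conclusion.** The concern holds in this limited form. Non-disclosure alone does not give the blinding that Section 6.2 asserts. At T2 the session content differs by arm through the training evaluation, and a visit third in time identifies a trained control to anyone who knows the visit number. With 30 per group, the first route exposes all 60 visits of the between-group contrast and the second exposes 30 visits used only in the within-control analysis.

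This assumes that the assessors run or see the 6.1.2 questionnaires, which is the plain reading of Sections 6.2 and 6.3 together but is not stated outright. Exposure is smaller for the eye-tracking primary outcome and greater for examiner-run secondary tests such as the mobility test. The bias cannot be sized from the document, so the assumed shifts in the working should carry no weight in judging importance. The change is worth making because it protects a property the trial claims, at almost no cost.

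**What to change.** - Take the expectations/evaluation questionnaire out of the assessors' battery. The patient completes it after all testing and returns it, sealed or by post, to the coordinator.
- Withhold both visit number and group from the assessors.
- Ask patients before each visit not to mention training to the assessor.
- Process eye-tracking files with group and visit masked.
- Reword Section 6.2 to claim only the blinding these steps achieve, and note that the third visit in time is unmasked if its number becomes known.

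The cost is an envelope, a change of order in the session and a short instruction to patients. The downside is a slight risk of missing evaluation questionnaires. No test or visit is lost.

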## 6.3. Study procedures

For the evaluation of inclusion, patients take part in a regular admission interview, visual function assessment, low vision assessment and neuropsychological assessment at Royal Dutch Visio in the nearest region. Participants will visit the UMCG two or three times (depending on the research group) for the effect measurements. The tests and assessments including in the effect measurements are described in section *6.1.2. Secundary outcome measures.*

## 6.4. Withdrawal of individual subjects

Patients are allowed to withdraw from the study without reason at any time, without any consequences for the individual patient. The researcher is allowed to remove patients from the study for medical reasons.

## 6.5. Replacement of individual subjects after withdrawal

In case of withdrawal, a new patient will be included.

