# 4. STUDY POPULATION

## 4.1. Population

The study population consists of 60 patients of Royal Dutch Visio with HVFD (hemianopia or quadrantanopia, existing for at least 6 months) due to acquired post-chiasmatic brain injury. Participants have no severe motor, perceptual and neuropsychological disorders. Mobility (percentage preferred walking speed), participation and quality of life are important dependent variables in this study. These variables might also be influenced by other disorders than the hemianopia, such as severe balance disorders, disorders of cognitive functioning or psychological disorders (e.g. panic disorder with agoraphobia). There are several reasons to exclude patients with such disorders from the study. First of all, the comorbidity prevents us from determining the effect of the intervention. Second, in case of such comorbidity, other rehabilitation approaches are often preferred to the scanning training protocol. Because only severe comorbidity is excluded, the included group is expected to be sufficiently heterogeneous to determine the (predicting) influence of factors such as intelligence, memory and executive functioning on the training effect. Almost all patients with hemianopia that were registered at Royal Dutch Visio in the last couple of years had injury to the primary and/or secondary visual cortex, mostly because of an ischaemic accident in the acp or posterior part of the acm. Disorders of executive functioning, aphasia, spatial disorders and memory disorders are often related to damage to more frontal regions and are relatively rare in this patient group. Although hemiparesis is often present in the acute stage, patients with hemianopia rarely present motor problems when seen for rehabilitation at Royal Dutch Visio.

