## 4.4. Sample size

The sample size was based on previous studies on the effect of CST. There is no reason to expect negative effects of training. Therefore, calculation of sample size was based on one-sided testing. Section *6.1.1 Primary outcome measures* provides more information on the reasons for eye movement parameters as primary outcome parameters. The Effect Size (ES) is calculated based on previous studies on the effect of CST on the number of fixations and refixations [2,5]. Taking the lowest value encountered (ES = 0.65), a minimum of 30 participants per group is required (training group vs. control group; two independent groups; α = 0.05; β = 0.20; one-sided testing). When comparing pre and post assessments within the total group (n=60), an ES of 0.34 can be detected with power 0.80 and one-sided testing with 0.05 significance. This means that even in case of low effectiveness of compensatory scanning training, the group size is fully sufficient. We assume an inflow of 120 patients (n=120) and we take into account a loss of 30 patients (25%) based on medical history (remaining n=90), 15 patients (17%) after assessment of inclusion and exclusion criteria (remaining n=75), and 15 patients (20%) during the period of training and effect measurements (remaining n=60).

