## 6.6. Follow-up of subjects withdrawn from treatment

Patients withdrawing from the study will be asked permission for the researchers to look into the available (para)medical data.

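### Replacing patients after allocation, with only records follow-up for those who withdraw, steers the analysed 60 towards patients who stayed

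*Protocol*

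**What the plan says.** All places are in the protocol.

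- **Section 3 (Design), step 5.** Allocation follows inclusion and consent, and comes before the effect measurements and training.
- **Section 6.5.** "In case of withdrawal, a new patient will be included". No time limit, arm or allocation rule is given for the new patient.
- **Section 6.4.** Patients may leave at any time, and "The researcher is allowed to remove patients from the study for medical reasons".
- **Section 6.6.** The heading is "Follow-up of subjects withdrawn from treatment". The text beneath it reads "Patients withdrawing from the study will be asked permission for the researchers to look into the available (para)medical data". Nothing else is provided for these patients.
- **Section 4.4.** The recruitment forecast ends with the loss of "15 patients (20%) during the period of training and effect measurements (remaining n=60"). The same section then treats the 60 as patients with both assessments: "When comparing pre and post assessments within the total group (n=60), an ES of 0.34 can be detected".
- **Section 6.1.1.** The primary outcome is fixation and saccade parameters from eye tracking on the Dot Counting Task, which is measured at the study visits in Groningen.
- **Section 8.2.** The between-group analysis compares T2 in the two arms, possibly corrected for T1. T2 is the post-assessment in the training group and the pre-assessment in the control group.

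The protocol does not say that patients are analysed in the group to which they were allocated.

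**The concern.** Allocation balances the groups as they stand on the day of allocation. If patients who leave later have no T2 measurement and new patients make up the number, then whoever supplies data has been selected partly by an event after allocation. The minimisation factors cannot correct for that.

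The loss may also differ between arms. In the 10 weeks being compared, one arm trains and the other waits. A control patient reaches T2 before training has begun and so cannot yet have left because of it, whereas a training patient can. Section 6.1.1 notes that controls receive no placebo intervention, so nothing makes the two experiences alike. If the training patients who leave are those who would have scored poorly, the comparison tilts towards training. Section 4.4 plans one-sided testing, so a tilt in that direction goes directly into the false-positive rate.

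The matter cannot wait for the SAP. A SAP can define an analysis set or impute, but it cannot recover eye-tracking data that were never recorded.

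**Working it through.** **1. The plan's own figures.** The forecast reproduces: 120 − 30 = 90; 90 − 15 = 75; 75 − 15 = 60, with 15/75 = 20%. The group size reproduces too. Section 4.4 states "Taking the lowest value encountered (ES = 0.65), a minimum of 30 participants per group is required", one-sided α 0.05, power 0.80. With 30 per group the noncentrality is 0.65 × √(30/2) = 2.517, the one-sided critical value of t on 58 degrees of freedom is 1.672, and the power is 0.800. So 60 is the number wanted with outcomes, and 75 is the number included to get there.

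**2. Following one withdrawn patient through the rules.**

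| Step | Rule | Result |
|---|---|---|
| Allocated, then withdraws | 6.4 | Leaves the study |
| Follow-up | 6.6 | Records only, with permission |
| Primary outcome | 6.1.1 | Needs a visit with eye tracking; T2 is missing |
| Vacancy | 6.5 | A new patient is included |
| Count towards 60 | 4.4 | Made up of those remaining |

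The missing T2 is what causes bias. If withdrawn patients kept a T2 measurement and stayed in the analysis, replacement would do little harm. If Section 6.5 were deleted and nothing else changed, 75 allocated with 15 lost would still leave 60 patients selected by staying. What replacement adds is a full count that conceals the loss.

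**3. Illustration of size.** None of these inputs is given by the protocol for this purpose:

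- Share of the training arm without T2: p = 0.20. This borrows the overall 20% of Section 4.4 and applies it to one arm, which is an assumption.
- Those lost would have scored δ SD worse than those who stayed: δ = 0.25, 0.5 or 1.0 (assumption).
- Control loss is unrelated to outcome (assumption).
- True effect zero, 30 analysed per group, no correction for T1.

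The mean of the whole training arm is (mean of stayers) − p × δ, so stayers alone overstate it by

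bias = p × δ.

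The type I error is the probability that a t variable on 58 degrees of freedom, with noncentrality bias × √15, exceeds 1.672.

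| δ (SD) | Bias (SD) | Share of ES 0.65 | Noncentrality | One-sided type I error |
|---|---|---|---|---|
| 0.25 | 0.20 × 0.25 = 0.05 | 8% | 0.194 | 7.3% |
| 0.5 | 0.20 × 0.5 = 0.10 | 15% | 0.387 | 10.3% |
| 1.0 | 0.20 × 1.0 = 0.20 | 31% | 0.775 | 19.0% |

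With half that loss (p = 0.10) the bias is 0.025 to 0.10 SD and the error 6.1% to 10.3%.

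**4. A second mechanism.** Suppose instead that the 20% with the worst prognosis leave the training arm only, and that prognosis correlates r = 0.3 to 0.5 with outcome (assumptions). The bias is r × φ(z₀.₂₀)/(1 − 0.20), that is 0.105 to 0.175 SD. By normal approximation the error is about 11% to 17%, the same order of magnitude.

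**The case against.** Several points on the other side carry weight.

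- **Replacement is not the cause.** This stands. The bias arises from missing T2 outcomes, so deleting Section 6.5 alone would not remove it. Section 6.5 also does not say that the new patient takes the vacated arm or must complete.
- **Double counting.** A reader might infer that the same loss is allowed for twice, once in the 75 and again through replacement. The protocol does not show this. Including 75 to finish with 60, and including a new patient for each withdrawal, can be one recruitment plan described in two places. No figure is inflated twice.
- **Stopping training treated as leaving the study.** A reader might infer this from Section 6.6, but it rests on the heading; the text speaks of withdrawing from the study. Sections 3 and 6.2 say that both groups attend a post-assessment, and no section says that a patient who stops training forfeits it. For someone who truly leaves the study, records by permission are normal. What remains is that the two events are never separated and that no section explicitly invites those who stop training to T2.
- **Motives of controls.** One might suppose that controls attend reliably because they are waiting for training. The protocol does not support that: withdrawal does not affect treatment, allocation does not change when training starts, and controls have three visits against two. Only the weaker statement holds, that loss may differ because the two arms do different things in the 10 weeks.
- **The 20%.** The 15 patients of Section 4.4 are lost across both arms and at any stage, possibly including controls after T2. Applying 20% to the training arm alone is an assumption. A T1 correction, which Section 8.2 leaves open, could absorb part of the bias.
- **The SAP.** The analysis set and the handling of missing data may be defined there. This stands for the missing-data model, but not for whether the T2 measurement is taken.

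**Conclusion.** The point holds as a defect in the rules for replacement and follow-up. Read together, Sections 6.5 and 6.6 leave withdrawn patients without a primary outcome and fill the analysed number with patients who stayed, so the between-group comparison is not fully protected by the allocation.

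It would go too far to say that the randomised comparison is lost, or that the plan prescribes an analysis of completers. No section defines such a set, and the bias could be small if withdrawals are few or similar in number and reason across arms.

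The size cannot be determined from the protocol. The range of 0.05 to 0.20 SD, with a one-sided type I error of about 7% to 19%, is conditional on all the assumptions listed with the calculation. It shows that the matter is worth settling; it does not predict the result.

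**What to change.** 1. **Section 6.5:** limit replacement to withdrawals before allocation.
2. **Section 4.4:** state that about 75 patients are allocated, as the forecast already foresees, so that 60 with outcomes are expected at 20% loss.
3. **Sections 6.4 and 6.6:** separate stopping training from withdrawing consent to assessments. Invite patients who stop training to the T2 visit at its planned date, and align the heading of 6.6 with its text.
4. **Section 8:** state that all allocated patients are analysed in their allocated group, with an analysis of completers as a sensitivity analysis only. Leave the missing-data model to the SAP.

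**Cost.** An amendment, and a few more attendances at a visit that is already planned and for which Section 9.5 reimburses travel. The assumed inflow of 120 does not change. The estimate may be smaller, because patients who stopped training are included. For example, if all 75 were analysed (37.5 per arm) and 20% of the training arm gained nothing (an assumption), the effect would be 0.65 × 0.80 = 0.52 and the power about 0.73 by normal approximation; at 10% it would be 0.585 and 0.81.
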